## 22.8 Survival Data

*All participants who consented to flagging with national registries have been flagged with NHS Digital.*

All men participating in the study who give their consent to record flagging (Consent 1 in the S1 PCC Schedule) will be flagged at the UK National Health Services Digital to ensure that the primary outcome of the study, time ascertained at 10 and 15 years, can be analysed. Notification of mortality and cancer incidence amongst study participants will be achieved through flagging and through links with hospital pathology and clinical services in the ProtecT catchments and participating GP practices. Clinical centre staff will return to the general practices to obtain the NHS number of those men who attended the PCC to allow automated flagging. Notifications from NHS Digital will be entered on the study database.

## 22.9 Extended Research Follow-up from 2018 to March 2022 and COVID-19 amendments

Participants diagnosed with prostate cancer will be followed up in four ways:

### 1. Passive follow-up by notification of vital status from national registries.

Notification from NHS Digital several times annually to central research team for participants who consented to central registry flagging. Vignettes created for cause of death committee to ascertain the underlying cause of death using medical record review at centres by trial staff from the research centre and OU. Death certificate data will be used to derive overall survival.

#### COVID-19 issues

University of Bristol (UoB, the research centre) closed their buildings (24th March 2020) preventing access to NHS Digital routine data due to the System Level Security Policy. Trial staff stopped note reviews at centres (16th March 2020, field work stopped by UoB).

#### Amendment

Cause of death committee suspended (24th March 2020).

### 2. Passive follow-up for clinical outcomes.

NHS routine data received several times annually by central research team. Outcomes will be derived from routine data by the central research team. Medical record reviews at centres will be targeted to supplement and validate routine data and will be conducted by research centre staff (UOB and UO) (and, if locally available, research staff at centres).

#### COVID-19 issues

UoB closed their buildings (24th March 2020) preventing access to NHS Digital routine data. Trial staff stopped note reviews at centres (16th March 2020, field work stopped by UoB).

#### Amendment

Urologist Principal Investigators to conduct medical record reviews by remote access to Trust Electronic Health Records (EHR). The CI confirmed with 8 of the 9 centre PIs that they had remote access and wished to help.

### 3. Participant questionnaires for patient-reported outcomes

A shorter questionnaire than previously is posted to participants annually from the research centre (MTQ13) up to and including 15 years of individual follow-up. A reminder is posted 4 weeks later and if there is no response the participant is telephoned by research centre staff around 2 weeks later if there is staff capacity. If

no questionnaire is received or telephone contact made a short version of the questionnaire (MTQ14) is posted at around nine weeks with a reminder two weeks later. All questionnaires can be completed online with the Research Data Capture (REDCap) system where up to three reminders are sent by email. There is a SOP (Follow-up of men : Part III Questionnaire follow-up).

#### COVID-19 issues

UoB shut their buildings (24th March 2020) except for tasks that could not be done remotely and on a limited basis. Returned paper questionnaires (MTQ13) are logged to generate reminders, make calls or send the short version (MTQ14).

#### Amendments

- Initial reminders might be later than 4 weeks.
- Telephone calls to remind participants might be later than 2 weeks after reminders and subject to capacity.
- The short version (MTQ14) may be later than 9 weeks than the original questionnaire.
- Telephone call by research centre staff to non-responders to offer to complete the questionnaire over the telephone as some participants may not be able to leave their homes.

#### 4. Participant interviews

A sample of participants in each treatment group and of non-randomised men already recruited to a qualitative sub-study will be interviewed if major prostate cancer disease events occur to evaluate men's experiences of outcomes and the implementation and acceptability of active monitoring. Interviews will be conducted either at UOB, or in men's homes or by telephone (as men prefer) by central research staff.

#### COVID-19 issues

UoB shut their buildings (24th March 2020) preventing interviews at UoB and visits to homes not possible, with staff capacity issues preventing interviews by telephone.

#### Amendment

Interviews paused (24th March 2020).

## **22.10 Extended Research Follow-up from April 2022 to March 2027**

### 1. Passive follow-up by notification of vital status from national registries.

Notification from NHS Digital to central research team for participants who consented to registry flagging. Vignettes created for cause of death committee to ascertain the underlying cause of death using medical record reviews at centres (or remote access to Electronic Health Record (EHR)) by research staff and, if available, with local PIs after median-20 year follow up reached. Death certificate data will be used to derive overall survival.

### 2. Passive follow-up for clinical outcomes.

NHS Digital routine data received by central research team. Outcomes will be derived from routine data by central research team. Medical record reviews at centres at end of follow up period targeted to supplement and validate routine data conducted by research centre staff (or remotely with EHR access), with local PIs.

### 3. Participant questionnaires for patient-reported outcomes until December 31st 2022

A shorter questionnaire posted to participants annually from the research centre (MTQ13) up to 15 years of individual follow-up. A reminder is posted 4 weeks later and if there is no response the participant is telephoned by research centre staff around 2 weeks later, if there is staff capacity. If no questionnaire is received or telephone contact made a short version of the questionnaire (MTQ14) is posted at around nine weeks with a reminder two weeks later. All questionnaires can be completed online with the Research Data Capture (REDCap) system where up to three reminders are sent by email. There is a SOP (Follow-up of men : Part III Questionnaire follow-up). Data collection will cease in December 2022.

## 23. CLINICAL FOLLOW-UP (CC)

*The treatment phase of the trial is completed and all participants are under the clinical care of their local NHS team.* Clinical follow-up will take place at 3-monthly intervals in the first year, and at clinical discretion thereafter. Clinical follow-up will be delivered by the specialist or their team (including the trial research nurses) undertaking the delivery of the treatment arms. These appointments will involve assessment of response to treatment, management of any complications, and investigation of any apparent disease progression. Any clinical follow-up is recorded as an event on the study clinical database in the follow-up module. Any PSA tests conducted in the radiotherapy arm up to 6 months post-treatment should be viewed with caution and the results may increase following cessation of hormone therapy.

## 24. OUTCOME MEASURES

*Trial outcomes remain unaltered in extended follow-up, unless stated below*

### 24.1 Primary Outcome

The primary outcome is definite or probable prostate cancer specific mortality (including definite or probable intervention-related mortality) at a median of 10, 15, and 20 years following randomisation.

### 24.2 Secondary Outcomes

- Overall survival at a median of 10, 15, and 20 years follow-up
- Other clinical outcomes at up to 10, 15, and 20 years follow-up: disease progression; treatment complications
- Urinary and bowel symptoms, quality of life, sexual function, depression and other psychosocial effects up to 15 years follow up

These outcomes will be evaluated in the following ways:

1. Prostate cancer mortality – An independent cause of death committee, blinded to the CAP allocation will be convened regularly to scrutinise vignettes and investigate/confirm the underlying cause of death.
2. Overall survival: cause of death from death certificates
3. Disease progression - using PSA, DRE, ultrasonography, biopsy, imaging.

4. Treatment complications – (immediate complications relating to primary radical treatments have been completed by 2017 whilst long term complications are ongoing) delayed treatment complications including (completed: blood loss), rectal/bowel (completed: injury/) symptoms, sexual dysfunction, (completed: urethral stricture), lower urinary tract symptoms and treatment, incontinence and obstruction, will be collected from routine data and in clinical schedules and Completed by 15 year analysis: participant questionnaires, developed in the feasibility study.
5. Participant questionnaire: General health status - measured by the validated instrument: EuroQol EQ-5D-3L. Completed by 15 year analysis.
6. Depression and psychological state - measured by the EORTC QLQ-C30 questionnaire completed at annually. Completed by 15 year analysis.
7. Urinary symptoms - measured by the ICSmaleSF questionnaire, which includes voiding and incontinence scores, nocturia, frequency and urinary-specific quality of life, the ICIQ questionnaire and items from the UCLA expanded prostate cancer index (EPIC). Completed by 15 year analysis.
8. Sexual function – measured by the UCLA EPIC. Completed by 15 year analysis.
9. Quality of life (QoL) related to prostate cancer treatment – measured using the UCLA EPIC. Completed by 15 year analysis.
10. Qualitative evaluation of outcome - assessed by in-depth interviews with samples of participants in each arm of the trial and also the preference groups. Completed by 15-year analysis:
11. Resource use (NHS, social service and personal). Routine hospital and primary care data sources with additional questions in clinical and participant questionnaires. Completed by 10 year analysis:

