| Primary Objective
Definite or probable prostate cancer specific mortality (and intervention-related mortality) at a median of 20 years following randomisation                                                                                                                                                                                                                                            | Ascertainment by independent cause of death committee using vignettes compiled from medical note reviews and routine data                                                                                                                                                                                                                                                                                                                                                                                                                                                                  | Ongoing

On notification of death                                                                                                                                                                                                                                  |
| Secondary Objectives
At a median of 20 years

Overall survival

Disease progression and metastasis

Treatment complications

General health status, quality of life, symptoms (urinary, sexual etc), depression and psychological state

Qualitative evaluation of outcome

Cost-effectiveness of treatments

Samples for basic science research (ProMPT) study | Death certificate data

Indicators of disease progression and complications of treatment from routine NHS data (PHE). Verification by clinical record reviews where necessary

Validated PROMs for symptoms/treatment complications: ICSmaleSF, ICIQ, EPIC; cancer-specific QoL: EORTC QLQC-30 and overall QoL: EQ-5D-3L

In-depth interviews with sample of participants in each arm and preference groups

Resource use from hospital and primary care and participant questionnaires

Annual blood sample (c. 50 mls) at NHS prostate cancer appointments | Ongoing (unless stated otherwise)

On notification of death

Routine data

Posted annually to participants or completed online up to 15 years' individual follow up or December 2022 when completed

Completed

Completed

Completed |

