## 7. STUDY DESIGN AND METHODS

The treatment trial consists of two major components:

- 1) Early detection of prostate cancer with participants invited from general practices to attend prostate check clinics to be informed about the uncertainties of treatment and the implications of testing
- 2) A three-arm randomised trial of treatment for participants with localised prostate cancer

The 10 year median follow-up was published in 2016. Extended follow-up will continue until March 2027 to allow a 20 year median analysis. Follow-up will be predominantly passive (routine data and medical note review) and is described in section 22.10. Participant questionnaires will cease to be collected at the end of 2022.

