### **2.10.2. Secondary outcomes**

Secondary clinical, economic and patient-reported outcomes to be presented in the primary results papers are:

- overall mortality
- metastatic disease
- primary treatment failure:
  - for radical prostatectomy: PSA 0.2ng/ml+ at three months post-surgery
  - for the radiotherapy protocol: according to the ASTRO criteria (Roach, 2006).
- clinical disease progression
- treatment complications
- resource use (the subject of a separate economic analysis plan)

*Metastatic disease* is defined as positive imaging showing bony, visceral and/or lymph node metastases, or PSA above 100; or bone marrow infiltration with associated systemic symptoms.

*Clinical disease progression* will be measured as person-years free of the consequences of disease progression. Signs of disease progression will include evidence of metastatic disease; the initiation of hormone therapy; diagnosis of clinical T3 or T4 disease; or ureteric obstruction, rectal fistula, or the need for a permanent catheter when these are not considered to be a complication of treatment.

The *treatment complications* listed in Table A will be recorded, following the indicated interventions. Complications following radical therapy will be presented irrespective of whether the man was allocated to that intervention, chose it following allocation, or it was recommended after a period of active monitoring.

The patient-reported outcomes which have been measured are listed in the Appendix. These measures are derived from validated questionnaires and have

been completed at recruitment, at first biopsy, six months after randomisation, and yearly thereafter for at least 10 years. These measures will be reported in a separate companion paper, to be submitted for publication at the same time as the primary outcomes paper.

**Table A.** Serious intervention-related complications occurring between intervention initiation and 90 days after intervention completion, which will be reported following the indicated interventions

|                                                        | Active monitoring protocol* | Surgery | Radiotherapy protocol |
|--------------------------------------------------------|-----------------------------|---------|-----------------------|
| Death                                                  | X                           | X       | X                     |

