### 2.9.2. Secondary outcomes

*Secondary clinical and patient-reported outcomes to be presented in the 15-year results papers are:*

- *overall mortality*

- *metastatic disease*
- *clinical disease progression*
- *initiation of long-term hormone therapy*
- *patient reported outcomes (PROMs)*

*Metastatic disease is defined as positive imaging showing bony, visceral and/or lymph node metastases, or PSA above 100; or bone marrow infiltration with associated systemic symptoms.*

*Clinical disease progression will be measured as person-years free of the consequences of disease progression. Signs of disease progression will include evidence of metastatic disease; the initiation of long-term hormone therapy; diagnosis of clinical T3 or T4 disease; or ureteric obstruction, rectal fistula, or the need for a permanent catheter when these are not considered to be a complication of treatment. There will be a review of cases where disease progression or metastatic disease are uncertain.*

As the ascertainment of clinical disease progression may differ between the three study arms, we will also present the initiation of long-term hormone therapy, to indicate those men whose disease is no longer curable.

The reporting of metastatic disease, clinical disease progression, and initiation of long-term hormone therapy is conditional on securing the data.

*The patient-reported outcomes which have been measured are listed in the Appendix. These measures are derived from validated questionnaires and have been completed at recruitment, at first biopsy, six months after randomisation, and yearly thereafter. These measures will be reported in a separate companion paper, to be submitted for publication at the same time as the primary outcomes paper.*

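### Treatment complications remain a stated outcome to 15 and 20 years, but no planned analysis covers clinically recorded late complications

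*Supplement*

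**What the plan says.** **The outcome.** Protocol v5.5, section 24.2, lists "Other clinical outcomes at up to 10, 15, and 20 years follow-up: disease progression; treatment complications". The synopsis places treatment complications among the secondary objectives at a median of 20 years. Section 6 lists them with no time limit, although it limits urinary, sexual and quality-of-life outcomes to 15 years. Section 24 opens by saying that outcomes are unchanged in extended follow-up unless stated, and item 4 of 24.2 describes long-term complications as ongoing.

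**The source.** Item 4 says that delayed complications "will be collected from routine data and in clinical schedules and Completed by 15 year analysis: participant questionnaires, developed in the feasibility study". The synopsis gives "Indicators of disease progression and complications of treatment from routine NHS data (PHE). Verification by clinical record reviews where necessary". For April 2022 to March 2027, section 22.10 says "Outcomes will be derived from routine data by central research team", with targeted record review at the end of the period.

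**What stops.** Section 7 says "Participant questionnaires will cease to be collected at the end of 2022". The 2022 update in section 3.1 leaves patient-reported outcomes (PROMs) out of the 20-year extension.

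**The analysis.** The 15-year SAP names treatment complications in its secondary objectives (2.1.2). Its section 2.9.2 then states "Secondary clinical and patient-reported outcomes to be presented in the 15-year results papers are" and gives five: overall mortality, metastatic disease, clinical progression, start of long-term hormone therapy, and PROMs. The 2015 SAP has one complication table, Table A, limited to "Serious intervention-related complications occurring between intervention initiation and 90 days after intervention completion". Protocol Appendix 2 says the 20-year analyses will be similar to those at 15 years.

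**The concern.** The protocol states a harm outcome for 15 and 20 years and names a source for it, but the analysis plan has no definition, summary, test or table row for it. If the plan is followed as written, the outcome goes unreported. The 20-year report would then set out mortality and progression by arm without the separate harm outcome that the protocol lists beside them. If the gap were filled only at reporting, the complications counted would be chosen with the data in hand, which is what a prespecified list is meant to prevent.

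**Working it through.** No power, alpha or event figure bears on this point. The check is a side-by-side reading plus date arithmetic.

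**1. Where complications appear**

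| Place | Clinically recorded complications? |
|---|---|
| Protocol synopsis, sections 6 and 24.2 | Yes, to a median of 20 years in the synopsis and up to 20 years in 24.2 |
| 15-year SAP 2.1.2, objectives | Named |
| 15-year SAP 2.9.2, outcomes to be presented | Absent |
| 15-year SAP 5.1, summaries | Absent |
| 15-year SAP 5.3, other analyses | Absent |
| 15-year SAP Table 1 | Absent: rows are prostate cancer death, any death, hormone treatment, progression, metastasis |
| 2015 SAP Table A | Present, closing 90 days after intervention completion |

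The 15-year SAP makes metastasis, progression and hormone therapy conditional on securing data. Complications are not listed even on that condition. Its progression definition also leaves out ureteric obstruction, rectal fistula and permanent catheter when these are judged to be complications of treatment, so events removed on that ground are then counted nowhere.

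**2. Does repeating the 10-year analysis fill the gap?** Appendix 2 says the 10-year analyses of primary and secondary outcomes will be repeated. Table A starts at intervention initiation and stops 90 days after completion, so repeating it adds early complications in men treated later. A complication arising years after treatment falls outside it for every man.

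**3. How far do PROMs reach?**
- SAP 5.3 tests PROMs by allocated group over 73 to 144 months; 144/12 = 12 years. SAP 5.4 adds effect modification for pad use, nocturia, erectile dysfunction and bloody stools.
- Median randomisation date: the SAP 5.2 census of 23 November 2020 minus 15 years = 23 November 2005.
- At the questionnaire stop (31 December 2022) the median man is 17.1 years from randomisation. His own questionnaires ended at 15 years.
- The last man was randomised in 2009. Because SAP 5.3 has all men at 12 years by 30 September 2021, I assume 1 January to 30 September 2009. He is then at 14.0 to 13.3 years at the stop, so some late entrants cannot reach 15 years of PROMs.
- Median 20 years falls on about 23 November 2025, which is 2.9 calendar years after the stop. For the median man the span without PROMs is 20 − 15 = 5 years.
- Protocol section 3.1 dates median 15 years to 23 November 2021 instead. The median man is then at 16.1 years at the stop, and his span without PROMs is still 5 years.

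**4. Section 24.2 against itself.** Its third bullet limits bowel symptoms and sexual function to 15 years. Item 4 puts rectal and bowel symptoms among the delayed complications still being collected, and continues "sexual dysfunction, (completed: urethral stricture), lower urinary tract symptoms and treatment, incontinence and obstruction, will be collected from routine data and in clinical schedules". The nurse-completed annual schedules of section 22.7 are not among the methods in 22.9 or 22.10, and section 27 has the clinical centres' database closed by 2018.

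**The case against.** The strongest reply is that late harms are analysed. Urinary, bowel and sexual effects make up most of item 4, and the 15-year SAP tests them as PROMs by allocated group, so monitored men who later have radical treatment are included. This stands to 12 years. It does not cover clinically recorded events, which 24.2 lists separately and carries to 20 years.

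Second, section 3.2 ties the trade-off to side-effects in the short and medium term and justifies 20 years by mortality and disease progression. This also stands, and it limits what is at stake. It does not withdraw the complication outcome that the synopsis and 24.2 still state at 20 years.

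Third, the SAP calls its synopsis background only, so section 2.1.2 is weak evidence of a conflict; it also repeats cost objectives that the protocol marks as completed. I accept that. The conflict rests on the protocol's outcome section against the SAP's outcome list and tables.

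Fourth, intervention-related death is in the primary outcome to 20 years. True, but it is not reported separately and covers only fatal harm.

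Fifth, no 20-year SAP is shown. That is correct: its content is inferred from Appendix 2, and there is still room to add the outcome.

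**Conclusion.** The point holds as a gap between a stated outcome and the planned analysis. At 15 years, clinically recorded complications are named in the protocol and missing from the SAP. From year 15 to year 20, no separately reported harm outcome has a planned analysis. The primary outcome is unaffected, so this should be corrected but does not threaten the main result.

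A reader might infer that the data sources have ended, or that routine data cannot measure the listed items, and so that the late-harm question cannot be answered. The documents do not support this. Routine data and record review continue to March 2027 and are the named source. Nothing in the documents says what those data can or cannot identify; they give only no complication definition, code list or validation. The stop to adverse event reporting from 2018 to March 2022 (section 22.2) does not settle the matter either, because item 4 does not name that reporting as a source.

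The conclusion rests on two assumptions: that the 20-year SAP will follow the 15-year one, as Appendix 2 says, and that Table A would be repeated, if at all, with its present window.

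**What to change.** 1. In the 20-year SAP, and in the 15-year tables where data allow, prespecify a set of late serious treatment complications identifiable in the routine data and record review already planned. Examples are coded procedures or admissions for urinary obstruction or stricture, incontinence, and bowel injury. Give the code list and the rule for record-review verification.
2. Report men with at least one event, and events per 1000 person-years, by randomised group from randomisation to the census date, as added rows in Table 1.
3. In section 24.2 item 4, limit patient-reported symptoms and sexual dysfunction to 15 years and delete clinical schedules as a current source. If stricture is in the set, change its completed label.
4. The sponsor should first confirm which routine fields are held. If they are inadequate, limit the stated complication outcome to the period actually covered, in the synopsis, section 6 and section 24.2.

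The cost is a code list, a verification rule and a few table rows, provided the fields are available. That is not established, since the SAP treats even metastasis data as still to be secured. The downside is that coded events miss milder complications and include some unrelated events in all arms.
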